#### Insulin requirements

2.10.2

During pre-project meetings, clinical teams noted that young people not using AID pumps do not routinely enter insulin data into their CGM systems. Therefore, at the baseline and 12-week visits, these participants will be instructed to prospectively record carbohydrate intake and insulin doses for the following 7 days. Daily carbohydrate intake and insulin doses, including basal insulin, rapid-acting boluses, correction boluses, and total daily insulin, will be collected and averaged over this 7-day period.

For participants using AID pumps, carbohydrate intake and insulin-dose data will be extracted from the corresponding pump software, regardless of device brand. Data will be obtained for the 7 days following each visit to ensure comparability with participants not using AID pumps. In addition, 14-day pre-visit data will be extracted for AID pump users and used in future within-group subanalyses.

#### Diabetes-related clinical characteristics and complications

2.10.3

Diabetes-related clinical characteristics will be collected from clinical records and the Diactive-1 web-based platform at baseline and, when applicable, at the 12-week assessment. These variables will include date of type 1 diabetes onset, diabetes duration, insulin delivery modality, use of multiple daily injections or insulin pump therapy, type of insulin pump, use of automated insulin delivery systems, CGM device type, type of rapid-acting insulin, type of long-acting insulin when applicable, prescribed carbohydrate intake, and current diabetes-related treatment characteristics.

Available information on diabetes-related complications will also be recorded from clinical records, including retinography results, nephropathy, or microalbuminuria status when available, and other clinically documented microvascular complications. These variables will be used mainly for baseline characterization, descriptive analyses, and exploratory subgroup analyses.

#### Cardiovascular biomarkers and lipid profile

2.10.4

Fasting blood and urine samples will be collected in the morning after an overnight fast of at least 12 h at the baseline and 12-week assessments, according to routine clinical procedures at each participating hospital. Samples will be processed in the corresponding hospital laboratory by technicians not involved in the project.

Core biochemical variables will include HbA1c (% and mmol/mol), serum glucose (mg/dL), lipid profile markers, renal-function markers, and urine albumin-related biomarkers. Specifically, when available, blood analyses may include urea and creatinine (mg/dL), total cholesterol, HDL-C, calculated LDL-C and triglycerides (mg/dL), ApoA-1 and ApoB-100 (mg/dL), albumin (g/L), liver enzymes (U/L), sodium and potassium (mmol/L), calcium (mg/dL), cystatin C (mg/L), and 25-hydroxyvitamin D (ng/mL). Urine analyses may include urinary microalbumin or albumin concentration, urinary creatinine, albumin-to-creatinine ratio when available, and routine urine-strip parameters. Complete blood count parameters will also be collected when available.

Given the multicenter pragmatic design, not all biomarkers may be available across all participating hospitals. Therefore, biomarkers will be analyzed according to availability and harmonized units, with core variables prioritized for between-group analyses and additional variables used for exploratory or descriptive analyses. Estimated glomerular filtration rate will be calculated using the bedside Schwartz equation, when serum creatinine is available, and expressed as mL/min/1.73 m² (40).

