In the 2026 Standards of Care in Diabetes, the American Diabetes Association (ADA) continues to recommend ≥60 minutes per day of moderate-to-vigorous physical activity and ≥3 days per week of muscle-strengthening activities for children and adolescents, recognizing exercise for the first time as an effective therapeutic strategy (20). However, a key challenge lies in enabling youth with type 1 diabetes to translate guideline-based recommendations into daily practice while understanding their individual glycemic responses to exercise. To address this gap, Diactive-1 was developed as an mHealth tool that leverages the widespread use of smartphones worldwide (21) to deliver tailored resistance training programs, responding to the limited evidence on the isolated effects of this modality (22), while incorporating glycemic monitoring around exercise to provide evidence-based recommendations (18). Our previous randomized clinical trial (RCT) conducted in Navarre, Spain, involving 62 youth with type 1 diabetes showed high usability of Diactive-1, with a score of 4.33 out of 5.00 (23), and demonstrated that participants allocated to the intervention group maintained glycemic stability while achieving significant reductions in daily insulin dose at 12 and 24 weeks compared with usual clinical care, with no reported hypoglycemic events (10). These benefits were accompanied by improvements in muscular strength, lean mass, and bone mineral content (24). Thus, Diactive-1 may have potential as an adjunctive tool to standard treatment by empowering youth to optimize daily type 1 diabetes management. However, the initial RCT was conducted in a single clinical context with a limited sample size, and the effectiveness of Diactive-1 across other hospital settings and clinical workflows remains uncertain. This could be addressed by scaling up Diactive-1 across multiple hospitals, incorporating an updated algorithm, refining the training program, and enhancing usability to promote greater engagement. Therefore, the primary aim of this multicenter randomized controlled trial is to evaluate the effectiveness of Diactive-1 (v2.0) in improving handgrip strength in children and adolescents with type 1 diabetes. Secondary aims are to examine its effects on glycemic stability, insulin requirements, cardiometabolic markers, physical literacy, quality of life, psychological well-being, and app-related engagement outcomes.

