### Primary outcome

2.9

The primary outcome will be the change in age- and sex-standardized handgrip strength z-score from baseline to 12 weeks. Handgrip strength was selected as the primary outcome because it is a feasible, standardized, and clinically practical indicator of muscular fitness that can be assessed consistently across participating hospitals and showed a significant between-group improvement in the previous single-center Diactive-1 trial (10). The trial will assess whether participants allocated to the intervention group show greater improvement in handgrip strength z-score than those allocated to the usual care group. Handgrip strength will be measured with the Takei III Smedley Type 297 digital dynamometer (Takei Scientific Instruments, Niigata, Japan), following The Youth Fitness International Test (YFIT) (35). Each participant will perform two maximal trials alternately with each arm, and the best value for each hand will be recorded. The average of the best right- and left-hand values will be used as the absolute handgrip strength value. Handgrip strength will then be standardized using FitBack^©^ sex- and age-specific reference values to obtain z-scores (30). Absolute handgrip strength in kilograms will be reported as a secondary outcome. This approach is supported by preliminary Diactive-1 trial findings showing a significant between-group improvement in handgrip strength z-score at 12 weeks (23).

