### Secondary outcomes

2.10

Secondary outcomes assessed in Diactive-1 are summarized in **Table 1**. Secondary outcomes are organized hierarchically in: key secondary outcomes (i.e., glycemic-stability parameters and insulin requirements); descriptive or contextual outcomes (i.e., sociodemographic information, diabetes-related clinical characteristics, anthropometric parameters, pubertal maturation, intervention engagement, and barriers to physical activity); and exploratory or hypothesis-generating outcomes, including cardiovascular biomarkers and lipid profile; lifestyle-related outcomes (i.e., 24-hour movement behaviors and adherence to the Mediterranean diet); physical-domain outcomes (i.e., self-reported physical fitness and physical literacy); mental and psychosocial outcomes (i.e., psychological assessments, health-related quality of life, and screening for eating disorders); and implementation-related outcomes intended to explore usability, acute glycemic responses, and potential dose-response relationships (i.e., app usability and data recorded by the Diactive-1 app).

**Table 1 T1:** Summary of the variables examined in the randomized clinical trial.

Primary outcome	Measurement	Tool
Handgrip strength	Directly: Objectively	- Takei III Smedley Type 297 digital dynamometer. - Age- and sex-standardized z-score calculated using FitBack^©^ reference values.
Secondary Outcome	Measurement	Tool
Glycemic stability	Indirectly: - Objectively	- CGM downloads. (without brand distinction)
Insulin requirements	Indirectly: - Objectively - Self-reported	- Insulin pump downloads. - Smart-pen logs. - Insulin records from participants using CGM. (without brand distinction)
Cardiovascular biomarkers and lipid profile	Directly: - Objectively	- Laboratory testing at each hospital’s central laboratory. (standardized protocols)
Anthropometric parameters	Directly: - Objectively	- Height: SECA 213 stadiometer. - Weight: SECA electronic scale.
Maturity status	Indirectly: - Objectively	- Peak height velocity: Moore’s equation. - Tanner scale.
Self-reported fitness	Subjectively: - Self-reported	- International Fitness Scale (IFIS)
Physical literacy	Subjectively: - Self-reported	- Spanish Perceived Physical Literacy Instrument (S-PPLI)

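### Section 2.10.4 fixes only a creatinine-based eGFR for a programme that may add muscle, so an arm difference could partly reflect creatinine production rather than filtration

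*Protocol article*

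**What the plan says.** - **Method.** Section 2.10.4 (Cardiovascular biomarkers and lipid profile) gives one rule for kidney function: "Estimated glomerular filtration rate will be calculated using the bedside Schwartz equation, when serum creatinine is available". No cystatin-C equation is given.
- **Place in the analysis.** The same section lists among its core variables "lipid profile markers, renal-function markers, and urine albumin-related biomarkers", and it plans the analysis "with core variables prioritized for between-group analyses and additional variables used for exploratory or descriptive analyses".
- **Alternative marker.** Cystatin C is in the list of assays that may be run when available. Section 2.10.4 says biomarkers will be analysed according to availability, so cystatin C is not excluded, but it is not named as the renal comparison.
- **Status.** Section 2.10 (Secondary outcomes) places this group under "exploratory or hypothesis-generating outcomes, including cardiovascular biomarkers and lipid profile".
- **Expected effect on muscle.** The Introduction says of the earlier trial: "These benefits were accompanied by improvements in muscular strength, lean mass, and bone mineral content". It gives no size for the lean-mass change.
- **Body composition.** Section 2.10.5 describes height, weight, BMI and maturity. It describes no lean-mass measure.

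**The concern.** Serum creatinine depends on how much the body produces as well as on how fast the kidneys clear it, and production follows muscle mass. This is general physiology; the protocol does not state it. At a given height, Schwartz eGFR is inversely proportional to creatinine. A training programme that adds muscle in one arm can therefore lower that arm's eGFR while filtration stays the same.

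The bias arises after randomization, in one arm, in a known direction, and it grows with any muscle gain. Randomization does not remove it. The Benjamini-Hochberg procedure in section 2.15 does not remove it either, because that procedure limits chance findings and not a systematic shift. As planned, nothing in the arm contrast for creatinine or eGFR separates the two explanations: no lean-mass measure is described, and no muscle-independent renal marker is designated for the comparison.

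What is at stake is the reading of one exploratory result in a population whose nephropathy and microalbuminuria status the trial records (section 2.10.3). The primary result is not affected.

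**Working it through.** **The plan's own figures.** The plan states no eGFR, creatinine or lean-mass figure, so there is none to reproduce on this point. The evaluable sample used below comes from section 2.4: 134 participants, 67 per arm. A two-sample t-test with d = 0.56 and 67 per arm gives 89.57% power against the stated 89.6%, and 134 / 0.85 = 157.6, which rounds up to 158. Both reproduce.

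**Inputs**
- From the protocol: 67 evaluable per arm; two-sided 0.05 (stated for the primary outcome, used here as the unadjusted level).
- Assumed, because the documents give nothing: a creatinine rise of 1-4% in the app arm only, eGFR 115 mL/min/1.73 m², and an SD of change of 12 mL/min/1.73 m² (15 and 20 also shown).
- Assumed form of the bedside Schwartz equation, which the protocol names but does not print: eGFR = 0.413 × height (cm) / creatinine (mg/dL). Only the inverse proportionality matters here.

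**Step 1: size of the artefact.** With height and true filtration unchanged, a creatinine rise of g lowers eGFR by 115 × (1 − 1/(1+g)):
- 1%: 115 × (1 − 1/1.01) = 1.14
- 2%: 115 × (1 − 1/1.02) = 2.25
- 3%: 115 × (1 − 1/1.03) = 3.35
- 4%: 115 × (1 − 1/1.04) = 4.42

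The starting point matters little. A 3% rise gives 3.4 at 140 cm and 0.50 mg/dL (eGFR 115.6), 3.1 at 155 cm and 0.60 mg/dL (106.7), and 2.7 at 170 cm and 0.75 mg/dL (93.6).

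**Step 2: precision.** SE of the arm difference = SD × √(2/67). With SD 12 this is 12 × √(2/67) = 2.07. An observed difference must reach 1.96 × 2.07 = 4.06 for unadjusted p<0.05. With SD 15 or 20 it must reach 5.08 or 6.77.

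**Step 3: false-positive rate.** The chance that a falsely lower app-arm eGFR reaches unadjusted two-sided p<0.05 is Φ(artefact/SE − 1.96). With no artefact it is 2.5% in that direction.

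| Creatinine rise | Artefact | Artefact/SE (SD 12) | SD 12 | SD 15 | SD 20 |
|---|---|---|---|---|---|
| 1% | 1.14 | 0.55 | 8% | 6% | 5% |
| 2% | 2.25 | 1.09 | 19% | 14% | 10% |
| 3% | 3.35 | 1.62 | 37% | 25% | 16% |
| 4% | 4.42 | 2.13 | 57% | 40% | 25% |

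**Step 4: fewer creatinine values.** Creatinine is collected when available, so the number analysed may be below 67 per arm. With an assumed 40 per arm and SD 12, SE = 12 × √(2/40) = 2.68, and the rates for 1-4% fall to about 6%, 13%, 24% and 38%. The size of the artefact does not change; only the chance of declaring it significant falls.

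**The case against.** The strongest case on the other side has five parts.

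- **It is exploratory and drives no decision.** This stands. A reader might infer that the plan would read a lower eGFR as renal harm. The documents do not support that. Section 2.10 calls these outcomes exploratory, and sections 2.12 and 2.14 do not make eGFR or creatinine a safety endpoint, a discontinuation criterion or a monitoring trigger.
- **eGFR is not itself named as core.** This stands as a limit. The eGFR sentence says only how it is calculated. That it falls under renal-function markers is an inference, though a natural one, since it is the only derived renal measure specified.
- **Other renal markers are already collected.** This stands in part. A reader might infer that cystatin C has no role, but it is to be analysed where available, and urine albumin-related markers are core. What is missing is a stated choice of which marker carries the arm comparison.
- **The muscle gain is unquantified.** This stands. The outcome the trial is built on is strength: "The primary outcome will be the change in age- and sex-standardized handgrip strength z-score from baseline to 12 weeks". The Introduction gives neither the size nor the timing of the earlier lean-mass gain. It would be too strong to say that any gain yields a visible signal; at a 1% rise the false-positive rate barely moves.
- **It could be left to the analysis plan.** This stands in part. Detail on an exploratory biomarker can sit there. But the protocol does not leave the method open: it fixes one eGFR equation and prioritizes the comparison, without a caution.

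The rates above are also unadjusted. The planned Benjamini-Hochberg correction within outcome families would lower them without removing the shift.

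**Conclusion.** The point holds as a minor weakness of interpretation. The protocol specifies a creatinine-based eGFR only, places renal-function markers among the variables prioritized for comparison between arms, and cites a lean-mass gain from the same programme. An arm difference in creatinine or eGFR could therefore partly reflect creatinine production, with a bias toward lower eGFR in the app arm.

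The direction is clear, but the size is not known. On the assumptions shown, the artefact is about 1.1-4.4 mL/min/1.73 m², with an unadjusted false-positive rate of about 8% to 57% at SD 12, and 5% to 25% at SD 20. Only the top assumption (4%, SD 12) makes a false signal more likely than not. No sample-size or power figure changes, and the primary outcome is untouched.

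**What to change.** In section 2.10.4:

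1. State that serum creatinine and Schwartz eGFR will be reported descriptively by arm and not interpreted as an effect of the intervention on kidney function, because creatinine also depends on muscle mass.
2. Prespecify cystatin C, or a cystatin-C eGFR, as the exploratory between-arm renal comparison in participants with the assay at both visits.
3. Report urine albumin concentration alongside the albumin-to-creatinine ratio, because urinary creatinine may also reflect muscle.

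The cost is a few sentences; no added test, visit or participant is needed. The downside is that the cystatin-C comparison covers only hospitals that already measure it, so it will be smaller and may not represent all sites. For that reason the first item matters most.

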#### Anthropometric parameters and stage of maturity

2.10.5

Standing height will be measured to the nearest 0.1 cm using a SECA 213 stadiometer, with participants barefoot, heels together against the base of the vertical column, back straight, and head positioned in the Frankfurt horizontal plane (41). Body weight will be measured to the nearest 0.1 kg using a SECA 869 electronic scale, with participants barefoot and wearing light clothing. BMI will be calculated as weight in kilograms divided by height in meters squared (kg/m^2^).

Peak height velocity (PHV) will be estimated using the Moore equation (42), and categorized as prepubertal (≤−1 year from PHV), peri-pubertal (−1 to 1 year from PHV), or post-pubertal (≥1 year from PHV) (43). Pubertal status will be assessed using Tanner criteria (44), which will be examiner-rated (i.e., physician-assessed) during the clinical visit.

#### Self-reported physical fitness

2.10.6

Self-reported physical fitness will be assessed using the International Fitness Scale (IFIS), a validated 5-item questionnaire evaluating perceived overall physical fitness, cardiorespiratory fitness, muscular fitness, speed–agility, and flexibility. The IFIS has shown good test–retest reliability (45). Each item is scored from 1 (“very poor”) to 5 (“very good”), with higher scores indicating better perceived fitness. The overall fitness item will be used as the global indicator, while the remaining items will describe specific fitness domains. If required, a composite IFIS score will be calculated by summing all five items, ranging from 5 to 25 points.

#### Physical literacy

2.10.7

Perceived physical literacy will be assessed using the Spanish Perceived Physical Literacy Instrument for Adolescents (S-PPLI), a culturally adapted and validated version of the Perceived Physical Literacy Instrument for use in Spanish adolescents. The S-PPLI has shown adequate construct validity and reliability (46).

The S-PPLI comprises 9 items across three 3-item factors. Each item is scored on a 5-point Likert scale from 1 (“strongly disagree”) to 5 (“strongly agree”). Factor scores are obtained by summing their three items, ranging from 3 to 15 points. The global S-PPLI score is the sum of all nine items, or the three factor scores, ranging from 9 to 45 points, with higher scores indicating greater perceived physical literacy.

The global S-PPLI score will be analyzed as a continuous variable, with factor-specific scores used to describe the three perceived physical literacy components. When categorical interpretation is needed, previously used cut-offs will classify participants as low (9–31), moderate (32–36), or high (37–45) perceived physical literacy.

#### Twenty-four-hour movement behaviors

2.10.8

*Physical activity:* Self-reported physical activity will be assessed using the Spanish versions of the Physical Activity Questionnaire for Children (PAQ-C) (47), and the PAQ for Adolescents (PAQ-A) (48), according to participants’ age. Children aged 8–12 years will complete the PAQ-C, while adolescents aged 13–17 years will complete the PAQ-A. Both questionnaires are self-administered 7-day recall instruments designed to estimate general moderate-to-vigorous physical activity. The Spanish PAQ versions have shown good test–retest reliability and reasonable criterion validity against accelerometer-derived physical activity.

The PAQ-C comprises 10 items, nine of which contribute to the global score and assesses leisure-time activity, physical education, recess, lunchtime, after-school and evening activity, weekend activity, overall weekly activity, and daily activity frequency. The PAQ-A comprises 9 items, eight of which are scored, and assesses the same domains except recess, which is omitted. In both questionnaires the final item identifies illness and is not scored.

Scored responses will be coded from 1 to 5, with higher values indicating higher physical activity. The leisure-time domain will be computed as the mean of the listed activities, and the daily-frequency domain as the mean of the seven weekday scores. Original PAQ scores will be calculated as the mean of all scored domains: nine for the PAQ-C and eight for the PAQ-A, as the adolescent version omits the recess domain. To harmonize both questionnaires, a common PAQ score will be derived from the eight shared domains.

*Screen time:* Screen time will be assessed using selected items from the Spanish version of the Health Behavior in School-aged Children (HBSC) questionnaire, a WHO collaborative cross-national study that uses standardized school-based self-report questionnaires (49). Participants will report their usual leisure-time screen use separately for weekdays and weekend days across three domains: television/videos, electronic games, and other electronic-device use. For each domain, average daily screen time will be calculated as a weighted mean of weekday and weekend use: [(weekday use × 5) + (weekend use × 2)]/7. Domain-specific estimates will then be summed to derive total leisure-time screen time. The HBSC screen-time items have shown acceptable test–retest reliability in adolescents, supporting their use for population-based surveillance of screen-based behaviors (50).

*Sleep time and efficiency:* Sleep will be assessed using selected items from the Pittsburgh Sleep Quality Index (PSQI) (51). Participants will report their usual bedtime, wake-up time, sleep-onset latency, and actual sleep duration during the past month. Sleep efficiency will be estimated as actual sleep duration divided by time in bed, multiplied by 100.

#### Barriers to physical activity

2.10.9

Perceived barriers to physical activity will be assessed using the Physical Activity Barriers Scale for pediatric type 1 diabetes (PABS-1), an 18-item self-administered questionnaire developed and validated in Spanish-speaking children and adolescents with type 1 diabetes (52). The PABS-1 has shown adequate psychometric properties in youth with type 1 diabetes aged 6–18 years. Content validity was supported by experts and the four-factor structure showed factorial validity. Test–retest reliability showed moderate-to-good stability for most items.

Items are scored on a 4-point Likert scale from 0 (“strongly disagree”) to 3 (“strongly agree”), with higher scores indicating greater perceived barriers. Total and domain-specific mean scores will be calculated across four domains: diabetes-related barriers, physical and health-related barriers, motivational barriers, and environmental and family-related barriers.

